## Methods and analyses

### Phase 1: establish content validity of the candidate items through cognitive interviewing

#### Design, sample, and setting

A 10-domain structure (Figure 1) and an initial pool of 50 items were constructed based on our prior concept elicitation study (Wiener et al., 2014). The PCSS (both child and caregiver-proxy versions) evaluates how much the child has been bothered by each symptom in the past 1 month. The 1 month recall period and the focus on the concept of symptom bother align the PCSS with the LSS, the measure used with respondents ages 18 and older. Symptom bother incorporates symptom frequency, severity, and interference with usual activities (Gawlicki et al., 2014). Responses are provided on a three-point scale incorporating a pictogram (for respondent’s ages 5–7 years) or a five-point Likert scale (for children ages 8–17 and caregiver-proxy respondents).

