##### Construct validity

For concurrent validity, we will examine the associations using Pearson correlation coefficients between the PCSS and the total and subscale scores of the PedsQL and PedsQL-SCTM. We will also examine associations between subscales of the PCSS and conceptually relevant items and domains of the PedsQL and the PedsQL-SCTM. We have pre-specified 25 comparisons between PCSS and the PedsQL, and PedsQL SCTM. To control for inflated Type 1 error, we will adjust for multiple comparisons using the Benjamini-Hochberg step-up method. The anticipated pooled sample size of 120 pediatric participants across the designated age cohorts (ages 5–7, 8–12, and 13–17 years) provides adequate precision for two-sided (1–0.05/25) % confidence intervals for Pearson correlation coefficients. With a sample size of 120 pediatric participants, the two-sided 99% confidence interval around a Pearson correlation of 0.8 is 0.70–0.87. Confidence interval calculations are based on a *z* transformation.

To evaluate known-groups validity, we will use independent samples *t*-tests (for two group comparisons), ANOVA (for three or more group comparisons), or Jonkheere-Terpstra tests for differences (for monotonically increasing comparison groups such as those created based on cGVHD severity scores). In evaluating known-groups validity, we will determine if mean item or mean subscale scores differ across relevant indicators of the respondent’s health status, quality of life, or clinical anchors such as NIH cGVHD severity score, NIH cGVHD organ-specific severity scores, and intensity of immunosuppression. Chi-squared tests will also be used to evaluate if the distribution of scores (range 0–4) differs between the known groups. Analysis for a clinical anchor will not be undertaken if it is observed prevalence is <20 or > 80%.

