We will also explore the congruence between symptom ratings provided by children and their caregiver-proxies, and examine the subscale structure using confirmatory factor analysis in children (pooling data across age cohorts to achieve a sufficiently large sample for the factor analysis). To evaluate child and caregiver-proxy congruence between symptom ratings, we will use weighted kappa with 95% confidence intervals to estimate the item-level agreement between the child’s severity rating and their caregiver-proxy’s severity rating for each symptom. Sensitivity analyses will compare the results of these pooled analyses with those derived from analyses within age cohorts, thus identifying age-related trends. Confirmatory factor analysis (CFA) will be used to explore the factor structure of the PCSS, based on the 10 domain constructs (skin, eyes, mouth, eating/digestion, lungs and breathing, muscles and joints, urogenital, energy, body image, and mood) hypothesized to underlie the PCSS. Fit indices [specifically root-mean-squared error of approximation (RMSEA), comparative fit index (CFI)] will be used to test the adequacy of the fit of the hypothesized 10-factor model to the observed data. Good model fit is indicated by RMSEA values <0.09 and/or CFI values greater than 0.90. The project sample size of 120 child respondents is likely too small to provide definitive results using CFA, however results will be informative toward the interpretability of subscale scores and will provide power estimates for a future definitive study powered to provide a robust evaluation of the PCSS factor structure.

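### The either-index fit rule (RMSEA <0.09 and/or CFI >0.90) can label a badly mis-specified 10-factor model as good fit on RMSEA alone when loadings are weak to moderate

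*Protocol article*

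**What the plan says.** In the protocol article, under Statistical analysis, Construct validity, the CFA is introduced as exploratory: "Confirmatory factor analysis (CFA) will be used to explore the factor structure of the PCSS". RMSEA and CFI are then to be used to "test the adequacy of the fit of the hypothesized 10-factor model to the observed data", and the decision rule is "Good model fit is indicated by RMSEA values <0.09 and/or CFI values greater than 0.90".

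The same paragraph limits the claim: "The project sample size of 120 child respondents is likely too small to provide definitive results using CFA". It still gives the result a use: "results will be informative toward the interpretability of subscale scores and will provide power estimates for a future definitive study".

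On the size of the model, Phase 1 (Design, sample, and setting) says "A 10-domain structure (Figure 1) and an initial pool of 50 items were constructed". Items may be eliminated during Phase 1, and the final count is not given.

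Subscales also appear earlier in Construct validity: "We will also examine associations between subscales of the PCSS and conceptually relevant items and domains". Those analyses are not made conditional on the CFA result.

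**The concern.** Under and/or, one index suffices, and the article does not say how to read a low RMSEA beside a low CFI. That combination is the likely one here. RMSEA spreads misfit over the degrees of freedom, and a 10-factor model of 30 to 50 items has several hundred to more than a thousand of them. When items load weakly or moderately, even a wrong structure produces little misfit per degree of freedom. CFI compares the model with a no-factor baseline, so it shows the problem, but the rule lets RMSEA override it.

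At stake is the meaning of a good-fit statement for ten subscales. If right and wrong item-to-domain assignments both pass, the statement cannot inform the interpretability of subscale scores, which is the use the plan gives it.

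**Working it through.** **Plan's own figure.** The article derives no figure for the CFA, so there is none to reproduce. The one interval it bases on N = 120 does reproduce (99% CI for r = 0.8, Fisher z): 1.0986 ± 2.576/√117 gives 0.697 to 0.871, against the stated 0.70 to 0.87.

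**Inputs.** From the article: 120 children pooled over age bands, 10 factors, an initial pool of 50 items, and the two cutoffs. Assumed, because not given: 30 or 50 final items, equal loadings of 0.4 to 0.8, equal factor correlations of 0.3 or 0.5, continuous normal items, maximum likelihood.

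**Degrees of freedom.**
- 50 items: 50 loadings + 50 residual variances + 45 factor correlations = 145 parameters; df = 50·51/2 − 145 = 1130; null-model df = 1225.
- 30 items: 105 parameters; df = 465 − 105 = 360.

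**What RMSEA <0.09 requires.** RMSEA = √[(χ² − df)/(df·(N − 1))], so χ²/df must stay below 1 + 0.0081 × 119 = 1.96.

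**What that allows for CFI.** With 50 items and a model exactly at RMSEA 0.09, CFI = 1 − (0.0081 × 1130)/(RMSEA_null² × 1225). This is 0.67 if the null-model RMSEA is 0.15, and 0.81 if it is 0.20.

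**Simulation, 200 samples of N = 120 per setting.** The truth is 10 correlated factors. The wrong model also has 10 factors, but its items are spread evenly over the wrong domains.

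| Items | Loading / factor corr. | Wrong model: mean RMSEA | Wrong model: mean CFI | Wrong model passes plan's rule | Correct model passes if both indices required |
|---|---|---|---|---|---|
| 50 | 0.4 / 0.3 | 0.049 | 0.398 | 100% | 0% |
| 50 | 0.5 / 0.3 | 0.061 | 0.423 | 100% | 1% |
| 50 | 0.6 / 0.3 | 0.078 | 0.422 | 100% | 4% |
| 50 | 0.6 / 0.5 | 0.066 | 0.628 | 100% | 10% |
| 50 | 0.7 / 0.5 | 0.086 | 0.604 | 81% | 68% |
| 50 | 0.7 / 0.3 | 0.101 | 0.411 | 1% | 54% |
| 50 | 0.8 / 0.5 | 0.115 | 0.556 | 0% | 100% |
| 30 | 0.5 / 0.3 | 0.055 | 0.580 | 100% | 47% |
| 30 | 0.6 / 0.3 | 0.078 | 0.540 | 95% | 74% |
| 30 | 0.7 / 0.5 | 0.089 | 0.706 | 55% | 99% |
| 30 | 0.7 / 0.3 | 0.106 | 0.499 | 0% | 97% |
| 30 | 0.8 / 0.5 | 0.125 | 0.644 | 0% | 100% |

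Every wrong-model pass came from RMSEA; CFI exceeded 0.90 in none. The correct model met RMSEA <0.09 in all samples of every setting. So where the wrong model passes 100% of the time, a pass is equally likely under either structure. At 81% and 55% the ratio is 1/0.81 = 1.2 and 1/0.55 = 1.8. Rates near the cutoff also depend on fitting details, such as whether factor correlations are constrained.

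**Not only a small-sample effect.** In the population (50 items, loadings 0.6, correlation 0.3), a one-factor model fitted to the 10-factor truth has RMSEA 0.067 and CFI 0.47. At 0.7/0.3 and 0.8/0.5 its RMSEA is 0.094 and 0.109, which fails.

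**Does a one-factor comparison separate right from wrong?** Ten factors use 45 more parameters than one, so for a lower BIC χ² must fall by more than 45 × ln 120 = 215. From the simulated mean RMSEAs, χ² ≈ df·(1 + 119·RMSEA²); the one-factor df is 1175 (50 items) or 405 (30 items).
- 50 items, 0.6/0.3: one factor (0.079) 2048; correct ten (0.041) 1356, a fall of 692; wrong ten (0.078) 1948, a fall of about 100.
- 50 items, 0.5/0.3: one factor (0.061) 1695; correct ten (0.040) 1345, a fall of 350; wrong ten (0.061) 1630, a fall of 65.
- 30 items, 0.6/0.3: one factor (0.077) 691; correct ten (0.029) 396, a fall of 295; wrong ten (0.078) 621, a fall of 70.
- 50 items, 0.4/0.3: one factor (0.050) 1525; correct ten (0.039) 1335, a fall of 190, short of 215.
- 30 items, 0.5/0.3: one factor (0.056) 556; correct ten (0.025) 387, a fall of 169, short of 215.

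In these settings BIC on average does not favour the wrong assignment. At the weakest loadings it can also fail to favour the right one.

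**The case against.** The strongest reply is that no decision hangs on the rule. The CFA is described as exploratory and not definitive, it is not in the stated Phase 2 primary objective, and the concurrent and known-groups analyses of subscales go ahead whatever the fit. Test–retest reliability and responsiveness use the total score. This stands. A reader might infer that the ten subscales would be supported by default, or that false support would flow into the other validity analyses. The text has no such mechanism.

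Second, passing depends on unknown loadings, and with strong items wrong models fail. This also stands, and it rules out saying that the rule accepts almost any structure.

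Third, simply replacing and/or with and would be a poor remedy. With 50 items and loadings of 0.6 or less, the correct model would pass in at most 10% of samples. This stands and shapes the fix.

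Fourth, estimator and model details may sit in the full protocol or analysis plan. That is fair for the estimator, but the pass rule is stated in the article and is itself too lenient. The sample-size caveat does not cure this, because it concerns precision, while the population values show the same weakness without sampling error.

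**Conclusion.** The point holds in a limited form. The stated rule lets RMSEA alone declare good fit. With 30 to 50 items and N = 120, that can label a badly mis-specified 10-factor model as good. This is near certain at loadings up to about 0.6, and happens in 55% to 81% of samples at loading 0.7 with factor correlation 0.5. It is rare or absent at 0.7 with correlation 0.3 and at 0.8 with correlation 0.5. Where it occurs, mean CFI is 0.40 to 0.63 with 50 items and 0.54 to 0.71 with 30.

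The consequence is confined to what a good-fit statement says about the subscales. The documents do not show that the subscales would be accepted by default or that another analysis would be corrupted.

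The figures rest on maximum likelihood, continuous items and equal loadings. PCSS items have three or five response points, so an ordinal estimator would give other index values, and the final item count is not given.

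**What to change.** Replace the either-index sentence with a rule that:

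1. reports RMSEA and CFI together and never calls fit good on RMSEA alone;
2. reports fit as inconclusive when RMSEA is below 0.09 but CFI is below 0.90. This should not count as rejection, because at N = 120 with about 50 items a strict both-indices rule would usually reject even a correct model unless loadings are about 0.7 or higher;
3. fits a one-factor model to the same data and describes the subscales as supported only if the 10-factor model fits clearly better, for example by lower BIC, or by a comparable criterion if an ordinal estimator is used. If it does not, report that support was not shown, since with weak loadings BIC can favour one factor even when ten are true.

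The cost is one extra model on data already planned and a few sentences of text. A good-fit statement becomes less likely. No change to sample size or data collection is needed.

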##### Reliability

For test–retest reliability, we will examine the level of agreement between total PCSS score at T1 and T2 using the Intraclass Correlation Coefficient (ICC) in all respondents, within 3–5 days of their initial completion. We will evaluate at T2 if by child and caregiver-proxy report the child remains in stable health and with stable symptoms of cGVHD (Qin et al., 2019). The ICC will be computed based on a two-way, mixed effects analysis of variance model (Shrout and Fleiss, 1979; Liljequist et al., 2019). ICC ≥ 0.70 will be interpreted as demonstrating adequate test–retest reliability.

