To inform the comparability of the PCSS and the LSS which is currently used with persons aged 16 years or older, respondents between the ages of 13 and 17 will complete both measures. We will use weighted kappa to estimate agreement between PCSS responses and responses to corresponding items from the LSS, in children between the ages of 13 and 17 and their caregiver-proxies. While this does not substitute for a full psychometric test of the equivalence of both versions, results will provide initial empiric estimates of the lowest age at which younger adolescents can meaningfully complete the LSS, and preliminary information about the comparability of PCSS and LSS values which may be useful toward justifying pooled analyses or interpreting outcomes specifically in trials of new cGVHD therapies when both the PCSS and the LSS are used. In subgroup analysis of respondents ages 13–17, we will examine the congruence between their symptom endorsement rates and their symptom severity ratings on the items of the PCSS and corresponding items in the LSS. This will inform our knowledge of the comparability of both measures in younger and older adolescents and derive preliminary estimates of the lowest age at which young adolescents can meaningfully complete the LSS.

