##### Responsiveness to change

To explore the responsiveness of the PCSS, study participants will be categorized into three groups based on responses to a question about their global impression of symptom change from baseline to 3 months (Coon and Cook, 2018). Within each group (no change, worsened, and improved), the total PCSS score will be compared used a paired *t*-test. The standardized response mean will be computed as the mean change scored divided by the standard deviation of the change scores within each change category (worsening vs. no change vs. improvement). Values greater than 0.8 will be considered large and values between 0.5 and 0.8 will be considered moderate. Subsequently the change in total score will be investigated using analysis of covariance in which the T1 score is a covariate and change in symptom severity (worsening vs. no change vs. improvement) is a factor in modeling the T2 rating. Lastly, change scores will be modeled using a generalized linear regression model. cGVHD severity scores and change in PedsQL physical function scores will be incorporated into this model in confirmatory analysis. These various approaches to examining responsiveness to change will be triangulated to preliminarily propose clinically meaningful thresholds for change at the individual and group level (Trigg and Griffiths, 2021).

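### Item-level weighted kappa does not quantify a systematic difference in level between PCSS and LSS, or between child and caregiver, and no signed total-score comparison is planned

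*Protocol article*

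**What the plan says.** All references are to the protocol article, Phase 2, Statistical analysis.

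- **Child against caregiver (Construct validity).** Congruence is explored with "weighted kappa with 95% confidence intervals to estimate the item-level agreement between the child’s severity rating and their caregiver-proxy’s severity rating for each symptom", pooled and then by age cohort. No other statistic is named.
- **PCSS against LSS, ages 13–17 and their caregivers (Construct validity).** "We will use weighted kappa to estimate agreement between PCSS responses and responses to corresponding items from the LSS". A second comparison follows: "we will examine the congruence between their symptom endorsement rates and their symptom severity ratings on the items of the PCSS" and on the corresponding LSS items. No statistic is named for it.
- **Intended use.** The result is offered as "preliminary information about the comparability of PCSS and LSS values which may be useful toward justifying pooled analyses", with the caveat "While this does not substitute for a full psychometric test of the equivalence of both versions".
- **Elsewhere the total is the unit of analysis.** Reliability examines the "level of agreement between total PCSS score at T1 and T2 using the Intraclass Correlation Coefficient (ICC) in all respondents". Under Responsiveness to change, "the total PCSS score will be compared used a paired" t-test within each change group.

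Neither agreement analysis includes a signed difference, limits of agreement or an ICC on a total or domain score.

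**The concern.** Weighted kappa summarises how far two ratings of one item disagree, relative to chance. It does not say in which direction. If caregivers score most items slightly above the child, or adolescents answer the LSS slightly below the PCSS, the differences add up in a sum while each item's kappa hardly changes. The protocol's own reliability and responsiveness analyses use the sum, and a sum or domain score is what a trial would most naturally pool. The named statistic is therefore poorly matched to the comparability question. The study could report respectable kappas item by item and still leave a sizeable offset between totals unmeasured.

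**Working it through.** **1. The plan's own precision figure.** The document gives one: n = 120, r = 0.8, 99% interval 0.70–0.87. By Fisher's z, atanh(0.8) = 1.099 and 2.576/√117 = 0.238. The limits are tanh(0.861) = 0.697 and tanh(1.337) = 0.871, so it reproduces. No precision is stated for kappa.

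**2. Inputs.** From the document: items scored 0–4 (Construct validity); five-point scale for ages 8–17 and caregivers, three-point for ages 5–7, initial pool of 50 items (Phase 1, Design, sample, and setting); 120 dyads, 40 of them aged 13–17 (Table 1). Assumed, because not given: 10–50 items; base-case item profile 60/18/12/6/4% for scores 0 to 4; latent reliability 0.8 (range 0.6–0.95); general-factor share 0.15–0.40; every item shifted in the same direction. The kappa weighting is not stated, so linear and quadratic are both shown.

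**3. Why kappa hardly moves.** With quadratic weights, kappa = 1 − E(X−Y)² / (σx² + σy² + δ²), where δ is the mean difference on the item. The numerator also contains δ², so a shift enters only as a square.

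Base-case item: mean 0.18 + 0.24 + 0.18 + 0.16 = 0.76; variance 1.84 − 0.76² = 1.262. Simulated kappa without shift is 0.711, so E(X−Y)² = 2 × 1.262 × 0.289 = 0.730. Holding the variances fixed:
- δ = 0.20: 1 − (0.730 + 0.040)/(2.525 + 0.040) = 0.700
- δ = 0.31: 1 − (0.730 + 0.096)/(2.525 + 0.096) = 0.685

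The total moves linearly: 30 items × 0.20 = 6.0 points.

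**4. Simulation, 30 items, reliability 0.8.**

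| Shift per item | Linear kappa | Quadratic kappa | Shift of total |
|---|---|---|---|
| 0 | 0.555 | 0.711 | 0 |
| 0.10 | 0.553 | 0.709 | 0.21 SD |
| 0.20 | 0.542 | 0.699 | 0.43 SD (6.1 points) |
| 0.31 | 0.523 | 0.680 | 0.67 SD (9.4 points) |
| 0.55 | 0.468 | 0.624 | 1.17 SD |

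The hand results agree closely. The small gap at 0.31 arises because the shift also changes the variance.

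**5. Can the drop be seen?** The approximate 95% half-width of one item's quadratic kappa in the base case is 0.20–0.22 at n = 40 and 0.12 at n = 120. The drop at 0.20 point is 0.711 − 0.699 = 0.012. At 0.31 point it is 0.031. The unshifted kappa is also never observed, so there is no reference value against which to notice a drop.

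**6. Sensitivity (10–30 items, reliability 0.6–0.95).**
- 0.2-point shift: quadratic kappa falls 0.004–0.022, linear by up to 0.04; total moves 0.30–0.59 SD.
- 0.31-point shift: quadratic kappa falls 0.012–0.05, linear by up to 0.08; total moves 0.46–0.91 SD.
- A separate run with 0.15–0.17 point gave a kappa drop of about 0.003–0.02 and a total shift of about 0.25–0.3 SD.

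**7. What a total-score comparison shows (base case).** The Pearson correlation of totals stays at about 0.945. Concordance of totals falls from 0.945 to 0.868 at 0.20 point and 0.787 at 0.31 point. The equal-SD approximation r/(1 + d²/2) gives 0.945/1.092 = 0.865 and 0.945/1.224 = 0.772. The paired mean difference has z of about 7 and about 10 at n = 40.

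**8. The endorsement comparison.** At n = 40 with 30 items, a 0.2-point shift raises endorsement by about 8 percentage points per item. Per-item power is about 17%, but about 82% of items lean the same way, and a test on summed endorsements would have power near 100%. No summing and no test is stated.

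**The case against.** The strongest points on the other side are these.

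- **This is an omission from a condensed article, in exploratory analyses.** Partly right: no stated number is wrong, and kappa is a standard choice for ordinal items. But the article itself names the statistic and the use it is meant to inform, so their match can be judged.
- **Item-level agreement is defensible.** It suits the question of the lowest age at which adolescents can complete the LSS, and the two instruments may not share all items. That stands. It is why the kappas should stay and why any PCSS–LSS sum should be confined to corresponding items.
- **Kappa is not the only PCSS–LSS comparison.** A reader might infer that it is. The document also compares endorsement rates, which are marginals and do move with a shift. An attentive analyst could notice a consistent lean, but the plan would not turn it into an estimate of the offset.
- **Kappa does respond to larger shifts.** A reader might infer that it never reveals one. At 0.55 point per item it falls by 0.04–0.09 at reliability 0.6–0.8, and at 0.95 by 0.13 (quadratic) to 0.20 (linear). One adolescent answering both scales at one timepoint may well sit at the higher end of reliability.
- **The article disclaims an equivalence test and sets no pooling or substitution rule.** Correct. That limits what is claimed, but it does not make kappa informative about level.
- **A constant offset need not bias a trial.** A reader might infer that pooling would bias the treatment comparison. The documents do not support that. The instruments are divided by age, so with arms balanced on age the offset cancels between arms, and it cancels within a patient who stays on one instrument. Bias needs imbalance of instrument or reporter by arm, or a switch during follow-up.

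**Conclusion.** The point holds in a limited form. Child–caregiver congruence rests on item-level weighted kappa alone. PCSS–LSS comparability rests on item-level weighted kappa plus an unspecified item-level comparison of endorsement and severity. Neither quantifies a systematic difference in level. Under the assumed profiles, a same-direction shift of about 0.15–0.35 point per item costs about 0.003–0.08 in kappa, mostly inside one item's sampling error at n = 40, while the total moves by about 0.25–0.6 SD or more.

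These sizes depend on the assumed number of items, score distribution and reliability, and on all items shifting the same way. Nothing in the document shows that such a shift exists. The conclusion is that the plan would not measure one if it did, although the planned data could. This is a worthwhile improvement to the analysis and does not invalidate the study.

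**What to change.** Keep the item-level kappas and state their weights. Add the mean signed difference with 95% confidence interval, the 95% limits of agreement, and an absolute-agreement ICC for:

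- **(a)** PCSS total and domain scores, child against caregiver, in ages 8–17, where both use the five-point scale (40 + 40 = 80 planned dyads);
- **(b)** the sum of corresponding PCSS and LSS items on a common range, in ages 13–17 (40 planned dyads).

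The ICC must be of the absolute-agreement type, because a consistency ICC or a Pearson correlation would ignore a constant shift. For ages 5–7, the child's three-point and the caregiver's five-point scale need a stated mapping before kappa or any total is compared. Base any preliminary statement on pooling on the mean difference and its limits, not on kappa alone.

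Cost: a few sentences in the analysis plan and a few table rows. No new data or participants are needed.
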